**Figure 3. f3:**
[figure not shown]
OneDraw blood collection kit.

The dried blood samples will be extracted at the University of Cambridge using a standard protocol for dried blood spots
^
29
^ and the lipid profile will be analysed using a combination of UHPLC and HRMS, and lipids will be quantified against internal standards as published previously.
^
22
^

Wearable camera technology

To effectively capture the dietary habits and food-related activities of individuals in UK households, a comprehensive passive dietary assessment system has been meticulously designed for this study. This system is a fusion of both hardware and software components, each with distinct functionalities to enhance the accuracy and efficiency of dietary data collection.

Hardware

For this pilot study, prototype of the camera was developed - wearable camera capable of recording up to 20hrs called M2.1. The wearable camera device is a high-definition camera with a maximum resolution of 2592x1944 pixels, mounted on the side arm of lens-less eye glasses frames to align with the user’s viewpoint and is connected to a rechargeable powerpack whilst in use (
Figure 4). It is designed to be used during daytime, capturing images of the eating process at frequency of one image every 1.5 seconds. The camera is powered by a built-in STM32 microcontroller with a 32-bit arm processor. The device begins recording upon the insertion of an empty 128 GB SD card and the camera is turned on. The camera is turned on automatically once is connected to the external battery.

**Figure 4. f4:**
[figure not shown]
Wearable camera equipment.

Prior to breakfast on day 1, participants received a camera device mounted on a glasses frame (or they can mount this on their own glasses frame) and were instructed to wear this until they went to bed, with the exception of when it is not suitable for the camera to be worn (such as when getting dressed and using the bathroom) in which case the glasses were be temporarily removed and details noted on the camera log. Upon arrival to the research unit on days 2-5, the SD cards were removed from the camera device by the research team and uploaded in duplicate to two encrypted external hard drives. Whilst the cameras were not in use overnight, participants were instructed to fully charge the power packs and start wearing the cameras the following morning before returning to the research unit (days 2-4).

Software

To ensure the anonymity of individuals, all footage captured by wearable cameras will undergo pre-processing prior to analysis. Initially, a large foundation model known as the Recognize Anything Model (RAM)
^
30
^ will be employed. RAM specializes in image tagging and has been developed through extensive training on a large number of general images. This model will play a crucial role in identifying images captured by our customised wearable camera. Its function will be to detect the presence of food items within these images. Upon detection of food items, RAM will assign a ‘food tag’ to the relevant images. This tagging mechanism is both efficient and precise, ensuring that only images with clear food content are marked for inclusion. The images that receive a ‘food tag’ from RAM will then be segregated from the rest and earmarked for further analysis, forming the core dataset for the study. Meanwhile, we have also designed ‘excluding tags’ for our model, which include around 20 categories of items such as bathrooms, mobile phone screens, and PC screens, with the flexibility to add or remove items as needed. This design is intended to prevent sensitive items from appearing alongside food in the collected data. Furthermore, for the retained images, an additional layer of protection will be implemented by blurring the faces of the participants and other individuals residing with them, as well as any other visible phone and computer screens that were unintentionally missed in the previous step. This step will use YOLOv8,
^
31
^ a deep learning technique renowned in the field of image recognition, to prevent the inadvertent disclosure of identities and personal information. Only after this pre-processing will the images be subjected to further analysis.

Following pre-processing is the food recognition phase, where we will leverage large language models (LLMs)
^
32
^ capable of processing both text and images. These models have been extensively trained on vast datasets, allowing them to recognize a wide range of food types without the need for additional training or fine-tuning. Portion size estimation also plays a pivotal role in dietary assessment, and our approach is tailored to address the unique challenges associated with using a wearable camera that captures only red-greed-blue (RGB) images, without the depth information provided by stereo imaging. This brings us to the issue of scale ambiguity, which is a significant problem given that our system cannot rely on stereoscopic methods to estimate the volume of food items. To circumvent the need for users to place a reference object next to their food - which would be an inconvenience and could disrupt a natural eating environment - we are exploring the potential of leveraging large-scale artificial intelligence (AI) foundation models to learn the general context of objects and their environmental surroundings in relation to food. By understanding these contextual relationships, the model can make more accurate inferences about the portion sizes of the food being consumed.

### Subjective dietary assessment tools

24-hour dietary recall

Participants completed a self-administered 24-hour dietary recall following each study day to measure both the accuracy of self-reporting and usability of repeated 24-hour dietary recalls. Participants used Intake24 (
intake24.com), which is a validated, web-based, open-source computerised dietary recall system based on the multiple pass method.
^
33
^ The tool, currently maintained by the University of Cambridge, Monash University and Newcastle University, is used by the UK’s National Diet and Nutrition Survey Rolling Programme.
^
25,
33
^ Participants used Intake24 to record everything they ate and drank the day before from midnight to midnight by using free text to list each food/drink item consumed per meal as part of the initial ‘quick list’. Next, the detailed pass stage involved searching Intake24’s food database for the closest match for each item then estimating their portion size using the images presented on the screen. Intake24 also prompted the participant about foods usually consumed together, e.g., if they recorded coffee then it will ask if they added milk and/or sugar, as well as frequently forgotten foods, such as condiments. Additional questions were presented if Intake24 identified long time gaps without food or very low energy intakes, and the recall ended with the participant reviewing their entries. Prior to completing Intake24 for the first time, participants were encouraged to watch the tutorial video (accessible via the Intake24 menu). At the end of the study, data was exported from Intake24 including the quantities and nutritional intakes for each food item recorded per recall, after which mean daily intakes per day per participant will be calculated.

FFQ

The eNutri web app, developed by researchers from the University of Reading, includes an FFQ based on UK diets.
^
34
^ The current version includes 157 food, drink and supplement items. For each food and drink item, users first select how often they consumed it during the previous 4 weeks from 10 frequency buttons (such as ‘not in the last 4 weeks’ and ‘once a day’). If consumed, they then select their typical portion size from 7 portion size photos/buttons. Certain items (n=37) also request additional details, for example, the type of milk (if any) added to their coffee and whether the item consumed was a low-fat or low-sugar variety (e.g., soft drinks, yogurts); each of these items also has an ‘I’m not sure’ option. Users also report frequency of use of salt (added at the table and/or during cooking) and 8 dietary supplements. Using this information, eNutri automatically calculates mean daily intakes (g/d) of each food item, from which it estimates a large range of food group intakes (e.g., vegetables, dairy) and nutrient intakes (e.g., protein, vitamin C). In addition to dietary intake, eNutri also records certain demographic and lifestyle information about the users (such as age, sex, ethnicity, education level, physical activity levels and smoking status).

For this study, participants used the eNutri FFQ tool on day 1 of study period 1 to measure their habitual diet by recording what they ate and drank during the previous 4 weeks. Prior to using eNutri for the first time, participants watched the short tutorial video on the web app. To measure dietary intake during the two 4-day study periods, a separate version of eNutri was created that adapted the frequency options to reflect 4 days of dietary intake (such as ‘not in the last 4 days’ and ‘1x in the past 4 days’). This was completed on day 4 of each study week.

### Participant feedback and usability of technologies

Participants completed the system usability scale (SUS) questionnaire following their first use of eNutri (day 1, week 1) and Intake24 (day 2, week1) via REDCap. The SUS questionnaire is widely-used to “measure people’s subjective perceptions of the usability of a system” and comprises of 10 alternating positive and negative statements regarding the user experience (
Table 4).
^
35
^ For each statement, respondents rate their agreement on a 5-response-scale from “Strongly Disagree” to “Strongly Agree” and, using the method described by Brooke (1995), a SUS score ranging from 0 to 100 is calculated, with higher scores indicating better usability.
^
36
^ Overall usability is also evaluated with a general question: “Overall, I would rate the user-friendliness of this system as:” with 7 options from “Worst Imaginable” to “Best Imaginable”.

**Table 4. T4:** SUS
* questionnaire.

1	I think that I would like to use this system frequently.
2	I found the system unnecessarily complex.
3	I thought the system was easy to use.
4	I think that I would need the support of a technical person to be able to use this system.
5	I found the various functions in this system were well integrated.
6	I thought there was too much inconsistency in this system.
7	I would imagine that most people would learn to use this system very quickly.
8	I found the system very awkward to use.
9	I felt very confident using the system.
10	I needed to learn a lot of things before I could get going with this system.

* System usability scale.

At the end of the study (day 4, week 2), participants also provided feedback about all of the tools used during the study. This included free text and Likert questions and were completed via REDCap.

### Statistical analysis

Previous studies have shown that the misreporting rate of total energy expenditure between self-reported dietary assessment tools and double labelled water was 35 % with a standard deviation of 33 %.
^
37
^ To reduce the misreporting rate to <10%, an
*a priori* sample size calculation determined that to achieve a power of 80 % with a type 1 error of 5%, a total of 27 participants are required. This was increased to 30 participants to account for potential dropouts. Two separate clinical research centres were used, with both centres recruiting participants to ensure consistent demographics between sites (sex, age, and BMI).

The FFQ data collected at baseline will be used to describe cohort demographics and serve as a covariate in analysis to account for differences in habitual dietary patterns among participants. Additionally, the data from 4-day FFQ will provide average dietary intake data for the two study weeks, which can be combined with daily aggregated data, such as Intake24. This data will be compared with metabolomic data and images to assess consistency and identify any biases. Such comparisons are crucial for evaluating the alignment of self-reported dietary data with objective biomarkers.

Bootstrapped Lin’s concordance correlation coefficient (CCC) with 95% confidence intervals will be used to test the extent of agreement between each dietary assessment tool/technology and the nutrient composition of known diets and recorded compliance.

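### The claimed 80% power with 27 participants belongs neither to the planned concordance analysis nor to the aim of misreporting below 10%

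*Protocol article*

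**What the plan says.** All the inputs stand in one paragraph of the protocol article, under Statistical analysis.

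- Misreporting in earlier work, self-report against doubly labelled water, "was 35 % with a standard deviation of 33" per cent.
- The aim of the calculation: "To reduce the misreporting rate to <10" per cent.
- The operating characteristics and the result: the calculation "determined that to achieve a power of 80 % with a type 1 error of 5%, a total of 27 participants are required". Then: "This was increased to 30 participants to account for potential dropouts".

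No test, sidedness, comparator or within-person correlation is given. The same section names the analysis: "Bootstrapped Lin’s concordance correlation coefficient (CCC) with 95% confidence intervals will be used to test the extent of agreement" between each tool and the composition of the known diets. No target CCC or interval width accompanies it.

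Under Randomisation, participants are allocated only to the order of the two diets. Under Study diets, everyone eats both. Under Primary and secondary outcomes to be measured, accuracy is judged against the known quantities of food given.

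**The concern.** The paragraph makes a complete, checkable claim: inputs, power, error rate and a total. Three things do not fit together.

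- **Design.** The figure of 27 comes out of a formula for two independent groups, or for pairs whose errors are uncorrelated. The trial has no parallel groups, and no pairing or correlation is stated.
- **Analysis.** The calculation concerns a shift in mean misreporting. The planned analysis estimates agreement with a CCC and its confidence interval.
- **Aim.** The wording sets a ceiling of 10%, whereas the arithmetic concerns detection of a 25-point difference from 35%.

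This is the article's only justification of sample size. The results are meant to guide a combined tool and a later free-living study. A reader could take it that the trial has 80% power to establish misreporting below 10%, which the stated SD does not support.

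**Working it through.** **Inputs.** Mean 35%, SD 33, target 10%, power 80% and type 1 error 5% are all from Statistical analysis. Two-sided testing is assumed unless stated otherwise. The difference is 35 − 10 = 25 points, so d = 25/33 = 0.758.

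**1. Reproducing 27.**

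- Two independent groups, normal formula: n = 2 × (1.960 + 0.842)² / 0.758² = 27.35 per group. That rounds up to 28 (29 by the t-test). With 27 per group the normal-theory power is 79.5%.
- Paired comparison with zero correlation: the SD of the difference is 33 × √2 = 46.7, and n = (46.7 × 2.802 / 25)² = 27.35 pairs. This is the same arithmetic, but here 27 would be a total. The paired t-test has 76% power at 27 and 81% at 30.
- One sample against a fixed 35%: n = (33 × 2.802 / 25)² = 13.7, so 14 (16 by the t-test). At 27 the t-test power is 97%, not 80%.

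Reading 35% and 10% as proportions does not give 27 either: about 43 per group for two groups, and about 23 for one sample.

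The figure therefore fits the two-group formula or its zero-correlation paired equivalent.

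**2. Power for a rate below 10%.** Test the mean against 10% with a one-sided 5% t-test, SD 33, one measurement per person. The noncentrality is (10 − true mean)/33 × √n.

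| True mean | n = 27 | n = 30 |
|---|---|---|
| 0% | 46% | 49% |
| 5% | 19% | 20% |
| 10% | 5% | 5% |

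The last row is the type 1 error alone. For 80% power on the same basis, 69 participants would be needed at a true mean of 0% and 271 at 5%.

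**3. Sensitivity of step 2.**

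- With n = 27 and a true mean of 0%, the power would be 81% if the SD were 20 instead of 33.
- Averaging two periods, with SD 33 per period and an assumed within-person correlation ρ, gives an SD of 33 × √((1 + ρ)/2). That is 23.3 at ρ = 0 and 31.3 at ρ = 0.8. At n = 30 and a true mean of 0% the power is then 74% and 53%; at a true mean of 5% it is 31% and 22%.

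**4. Precision at n = 30.** The 95% half-width for one period is t(0.975; 29) × 33/√30 = 2.045 × 6.02 = 12.3 points. Averaged over two periods it is 12.3 × √((1 + ρ)/2): 8.7 at ρ = 0 and 11.7 at ρ = 0.8.

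**5. The CCC.** Nothing in the calculation refers to it: no expected CCC, lower bound or interval width. A Fisher-z interval for a CCC of 0.80 with n = 30 would be 0.62 to 0.90, but it assumes 30 independent bivariate-normal pairs. Here everyone eats the same fixed menus and is measured repeatedly. A simulation of 30 people on two fixed diets, with a CCC near 0.8 and error correlations of 0 to 0.8, gave a sampling range of about 0.73 to 0.87. The Fisher-z figures are not a safe substitute.

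**The case against.** **The origin of 27 is not proven.** This stands. No test is named, and the two-group formula strictly rounds to 28. A paired t-test with 27 people reaches 80% at a within-person correlation of about 0.09, and with 30 it has 81% at zero correlation. A reader might infer that a per-group number was mislabelled as a total and that the trial needed 56 people. The documents do not support this: the trial has no independent groups, and a paired reading makes 27 a genuine total. The full protocol listed under Data Availability is not shown and may name the test. Even so, a paired comparison of mean misreporting is not the CCC analysis in the article.

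**The sample may be ample.** Against a fixed 35% it is, with 97% power at 27. The objection removes any claim that the trial is too small to show a difference from 35%. It does not make the stated 80% correct.

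**The SD may not apply.** This also stands. The 33% comes from self-report against doubly labelled water. Here the comparator is supplied food under controlled feeding, with two periods per person. A reader might infer that the trial cannot show misreporting below 10%. That goes too far: the power is low only under the stated SD and one measurement per person, and both may be more favourable in practice.

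**No decision rests on the 80%.** Recruitment and data collection are complete, the analysis is estimation, and 10% is not listed as a hypothesis to be tested. This limits the consequence to the claim itself, which is still published as the reason for the sample size.

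**Conclusion.** The point holds as a mismatch between the stated power and everything it should support. The 80% with 27 corresponds to a two-group comparison of means or a zero-correlation paired comparison, as far as can be inferred. It was not derived for the CCC of each tool against known intake. It also does not describe the chance of showing a rate below 10%. That chance is 46% to 49% at a true rate of 0% and 19% to 20% at 5%, given SD 33%, one measurement per person and a one-sided 5% test. The arithmetic is certain given these inputs. The formula behind 27 is an inference, and the size of the shortfall depends on an SD borrowed from a different comparator.

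**What to change.** Keep the 30 participants and rewrite the sample-size paragraph.

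- Withdraw the claim of 80% power and the claim about reducing misreporting to below 10%.
- State that the sample size was not derived for the CCC.
- Give the expected precision with its conditions. Suggested wording: *With 30 participants and an assumed SD of 33%, the 95% confidence interval for mean percent misreporting per tool has a half-width of about 12 points for one period, or about 9 to 12 points averaged over two periods for a within-person correlation between 0 and 0.8. The sample size was not derived for the concordance analysis.*
- Do not insert the Fisher-z interval of 0.62 to 0.90. Base any statement of CCC precision on a simulation or a bootstrap that resamples participants, reflecting the fixed menus and repeated measurements.

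The cost is one paragraph of text, plus a short simulation if CCC precision is to be quoted. No participants are added. The stated claim becomes less favourable. According to Study status the analysis was still in progress at submission, so the correction can precede the results.

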### Randomisation

After the pre-study visit, participants were assigned a study ID code and randomisation was undertaken using REDCap. Participants were randomly allocated to one of two diet orders: Diet 1 followed by Diet 2 or Diet 2 followed by Diet 1. Randomisation was stratified by study centres. The research team and participant was not be blinded to the randomisation, as study menus were provided in advance, making it clear which diet they would follow each week.

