### Study diets

Participants consumed two controlled diets, one per study period, provided in a random order: Diet 1: non-compliant with UK dietary guidelines (e.g., high in saturated fat, free sugars, and salt and low in fibre); Diet 2: compliant with UK dietary guidelines, e.g., within the dietary reference values for saturated fat (≤10% total energy (TE)), free sugars (≤5 %TE), salt (≤6 g/d) and fibre (≥30 g/d) (
Table 1). The diets were matched for energy, protein, total fat and carbohydrate. Foods and drinks selected for each diet were selected to allow investigation of specific biomarkers.
^
21
^ Each diet consisted of a 2-day repeating menu (e.g., menu A served on days 1 and 3, and menu B served on days 2 and 4) as shown in
Tables 2 and
3. Bottled spring water was also be available to drink throughout the day. Meals and snacks were consumed at 2-hour intervals throughout the study days (9 am breakfast, 11 am morning snack, 1 pm lunch, 3 pm afternoon snack, and 5 pm dinner) and were served using identical tableware at each research unit (white crockery and clear glass on days 1 and 2 and patterned crockery and coloured glass on days 3 and 4); no foods/drinks were consumed directly from their packaging. Participants were also provided with a snack and bottled water to take home to consume before 8 pm and instructed not to eat or drink anything else before returning to the research unit the following day.

**Table 1. T1:** Nutrient composition of the study diets
*.

Nutrient	Diet A	Diet B
Energy (kcal/d)	2291	2168
Protein (%TE)	14.8	14.3
Total fat (%TE)	35.6	35.6
Saturated fat (%TE)	16.4	5.7
Carbohydrates (%TE)	46.8	43.5
Free sugars (%TE)	13.6	4.6
Dietary fibre (AOAC) (g/d)	21.8	38.8
Salt (g/d)	7.6	5.6

* Mean of menu 1 and menu 2 per study diet.

**Table 2. T2:** Study menus for diet 1.

Menu	Menu items and quantities

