### Study visit procedures

The day before starting each study period, participants were asked to restrict their caffeine and alcohol intakes and exercise levels to amounts that were usual for them and fast for 12 hours overnight (not consuming any food or drink, except water). Upon waking, participants also collected a first morning void (FMV) urine sample.

Participants attended the research unit at 8 am on day 1 (Monday) of each study period. Upon arrival, blood pressure, height and body weight were measured. A fasted capillary blood sample (OneDraw) was also self-collected and participants were set up with the wearable camera (which was worn continuously except if participants used bathroom) before being provided with breakfast. Habitual diet was recorded using the eNutri tool (4-week version). With the exception of mealtimes, participants had the rest of the day as free time but remained in the research unit. At the end of the study day (6 pm), participants were provided with bottled water and a snack for the evening, urine kits (for last evening void (LEV) and FMV samples) and a reminder checklist/log. Days 2-4 repeated day 1 except: 1) Intake24 was used on days 2-4 to record dietary intake during the previous 24 hours, 2) 4-day version eNutri was repeated at the end of day 4 (Thursday) to record dietary intake during the previous 4 days, and 3) capillary blood samples were not collected on day 3 (Wednesday). On day 5 (Friday), participants collected a final FMV, completed Intake24 and returned samples/equipment to the research unit.

Participants’ compliance to the study protocol was recorded by study investigators during the times when they were in the controlled environment. For the times spent outside the research unit, compliance was measured using sample/data collection records and self-reported deviations to study menus.

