### Primary and secondary outcomes to be measured

The primary outcome will be the accuracy of dietary reporting, measured at the end of each intervention week using the known quantities of consumed foods given to participants during the intervention days and dietary data collected from wearable cameras, spot urine samples, capillary blood samples, and self-reported dietary assessments.

Secondary outcome measures include: 1) the creation of a multiplatform model of dietary intake using g/day measured from wearable cameras and self-report dietary assessments, and μg/ml of dietary exposure biomarkers from spot urine samples and capillary blood samples at the end of the study, and 2) the design of a dietary intake study in a free-living population that will be informed by the results of the current dietary intake study protocol.

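### With fixed menus, a Lin's CCC against known diet composition mostly measures the gap between the two diets, can mask or reward diet-specific misreporting, and has no stated resampling unit

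*Protocol article*

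**What the plan says.** The only agreement statistic that the Statistical analysis section names is "Bootstrapped Lin’s concordance correlation coefficient (CCC) with 95% confidence intervals". Its target is "agreement between each dietary assessment tool/technology and the nutrient composition of known diets and recorded compliance". That sentence mentions neither diet, period, centre nor clustering, and does not say what the bootstrap resamples. The only covariate mentioned in the section is the baseline FFQ.

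The design features that bear on this are:

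- **Reference.** Under Study diets, "Each diet consisted of a 2-day repeating menu". Energy, protein, total fat and carbohydrate were matched between the diets. Table 1 gives one mean composition per diet.
- **Repeated data.** Everyone takes both diets in random order. Under Study visit procedures, "Intake24 was used on days 2-4 to record dietary intake during the previous 24 hours", and on day 5 "participants collected a final FMV, completed Intake24 and returned samples/equipment to the research unit". That makes four recalls per period and eight per person. The 4-day FFQ is completed once per period.
- **Level of the primary outcome.** It is "measured at the end of each intervention week", so two values per person.
- **Randomisation.** "Randomisation was stratified by study centres", and "study menus were provided in advance, making it clear which diet they would follow each week".

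**The concern.** The CCC scores agreement relative to the spread of the reference values. It suits a reference that varies widely between subjects. Here everyone is served the same food, so almost all the spread is the contrast between Diet 1 and Diet 2. A coefficient computed within one diet has almost nothing to work with, and one computed over both diets depends on how far apart the diets happen to be in that nutrient.

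This matters because the Introduction gives under-reporting of socially undesirable foods as a reason for the study, and the trial randomises the order of a guideline-compliant and a non-compliant diet. Whether a tool errs more on the non-compliant diet is a question this design can answer within person. The named statistic cannot show it. Tools would also be ranked differently by nutrient for reasons unrelated to their accuracy.

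The second issue is the interval. In its standard form Lin's CCC assumes independent pairs, and these pairs are not independent.

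**Working it through.** The article gives no CCC value or interval width to reproduce. The section's only sample size figure is 27, which is close to 2 × (33/25)² × (1.960 + 0.842)² = 27.35. That formula compares two mean misreporting rates and says nothing about the precision of a CCC.

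**Formula.** CCC = 2·cov(x, y) / [var x + var y + (mean x − mean y)²], where x is the reference and y the tool.

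**Inputs from Table 1.** Fibre 21.8 and 38.8 g/d; saturated fat 16.4 and 5.7 %TE; salt 7.6 and 5.6 g/d; energy 2291 and 2168 kcal/d. I take Diets A and B in the table to be Diets 1 and 2 in the text, which fits their saturated fat, fibre and salt values.

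**Assumptions not in the documents.** The reference is constant within a diet, and the SD of the weekly error is 25% of the true value. I repeat the main results at 33%, the SD that the article quotes for misreporting.

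**Within one diet.** If x is constant, cov(x, y) = 0 and the CCC is 0 whatever the tool's accuracy.

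**Both diets, fibre.** var x = ((38.8 − 21.8)/2)² = 72.25. Error variance = 0.25² × (21.8² + 38.8²)/2 = 61.90.

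- Bias -15% on both diets: tool means 18.53 and 32.98; cov = 8.5 × 7.225 = 61.41; var y = 52.20 + 61.90 = 114.10; squared mean difference 4.545² = 20.66. CCC = 122.83/207.00 = **0.59**.
- Bias -30% on Diet 1 and 0% on Diet 2, the same average percent bias: tool means 15.26 and 38.8; cov = 8.5 × 11.77 = 100.05; var y = 138.53 + 61.90 = 200.43; squared mean difference 3.27² = 10.69. CCC = 200.09/283.37 = **0.71**.
- No bias at all: 144.50/(72.25 + 134.15) = **0.70**.

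A tool that misses 30% of the fibre on one diet therefore scores as well as an unbiased one, because the error stretches the between-diet gap. At an error SD of 33% the first two values are 0.49 and 0.61.

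The direction depends on the nutrient. For saturated fat, which is higher on Diet 1, the same change shrinks the gap and the CCC falls from 0.79 to 0.59.

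**Both diets, energy.** var x = 61.5² = 3,782. Error variance = 0.0625 × (2291² + 2168²)/2 = 310,903.

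- Bias -15%: 6,430/(3,782 + 313,636 + 111,840) = **0.015**.
- No bias: 7,565/(3,782 + 314,686) = **0.024**.

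At an error SD of 33% these are 0.010 and 0.014. At a common bias of -15% and SD 25%, the four nutrients score 0.79 (saturated fat), 0.59 (fibre), 0.31 (salt) and 0.015 (energy). The tool has the same percent error throughout; only the gap between the diets differs.

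**Interval coverage (simulation).** 30 participants, two diets, 400 replicates, 400 percentile bootstrap samples, bias -15%, within-person correlation of error 0.6, nominal 95%. Error SD is 33% for daily rows and 25% for weekly rows. Monte Carlo error is about 1 to 2 points.

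| Data | Nutrient | Rows resampled: coverage (width) | Participants resampled: coverage (width) |
|---|---|---|---|
| 8 daily rows | Saturated fat | 81.5% (0.124) | 93.8% (0.175) |
| 8 daily rows | Fibre | 82.8% (0.155) | 91.8% (0.210) |
| 8 daily rows | Salt | 88.0% (0.139) | 92.5% (0.162) |
| 8 daily rows | Energy | 99.3% (0.034) | 90.0% (0.025) |
| 2 weekly rows | Saturated fat | 93.5% (0.182) | 90.3% (0.165) |
| 2 weekly rows | Fibre | 92.0% (0.266) | 90.3% (0.247) |

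With daily rows and a correlation of 0.3, row coverage for saturated fat is 87.5%. At zero correlation it is 96%.

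**The case against.** The strongest reply is that the article does not say that days, periods and diets are pooled, or that rows are resampled. It condenses a fuller protocol that is not shown, and a CCC bootstrapped by participant is still a bootstrapped CCC. This stands for the resampling unit: the text is open, not wrong. It does not answer the first issue, because the fixed menus are in the article and leave a CCC against known composition little to work with unless the diets are combined.

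A reader might infer that the intervals are too narrow. The documents do not support that as a general statement. The end-of-week outcome and the 4-day FFQ point to weekly values, for which row resampling does not narrow the interval. For energy, row resampling makes it too wide. A design effect of 1 + 7 × 0.4 = 3.8, whose square root is 1.95, would concern the mean error over eight days at an assumed correlation of 0.4; it does not apply to the CCC.

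A reader might also infer that advance menus and repeated servings inflate the self-report results. That is possible, but its size cannot be derived from the article. A shift in bias from -25% in the first period to -5% in the second moves the CCC only from 0.79 to 0.77 for saturated fat and from 0.59 to 0.57 for fibre. So the CCC would not reveal practice, but that is no evidence that practice occurred.

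Two further points stand. The section also plans comparisons between tools to find biases, so the CCC is not the whole analysis. And percent error does not suit biomarkers measured in μg/ml.

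**Conclusion.** The point holds in two parts of unequal strength.

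The firmer part is the choice of statistic. With fixed menus, a CCC against known composition mainly reflects the between-diet gap. It can mask diet-specific misreporting or reward it (fibre 0.59 to 0.71), and for energy it is about 0.02 whether the tool is unbiased or 15% low. This rests on a reference nearly constant within each diet and on the assumed error SD; at 33% the pattern is the same. Recorded deviations, and at day level the difference between menus A and B, would add some spread to the reference. The article gives the size of neither.

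The weaker part is the interval. The resampling unit is unstated, and resampling rows could give coverage from about 80% to over 99%, depending on nutrient and row level. These figures depend on the assumed correlation, bias and SD. Participant resampling is right for the dependence, although with 30 people its percentile intervals also fall somewhat short, at about 90% to 94% here.

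The analysis should be changed, but nothing in data collection is affected.

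**What to change.** 1. State that the bootstrap resamples participants within centre, keeping all of a person's days and both periods together. State also whether the CCC uses daily or weekly values.
2. For tools that give intakes in g/day or nutrients, report next to the CCC the mean percent error with limits of agreement for each diet, and the within-person difference in error between diets. Take these from a mixed model with diet, period and centre as fixed effects and participant as random effect. Computing the CCC separately by diet is no substitute, since it is near zero by construction.
3. Present the CCC with the between-diet gap for each nutrient, and do not use it to judge accuracy for the matched nutrients.
4. First versus second serving of a menu may be added as a sensitivity analysis for Intake24. It should not become the headline, because the primary outcome is defined at the end of each week and data collection is already complete.

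The cost is wording, some code and a little more reporting. Some intervals will become wider. No new data are needed.
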